### Interventions

2.7

In the S-1 group, S-1 was given orally twice daily at a dose of 80 mg/m^2^/d after a meal for 14 consecutive days, followed by 7 days of rest, and every 21 days counts as a cycle.

In the S-1 combined with XSLJZD group, S-1 was given orally twice daily at a dose of 80 mg/m^2^/d after a meal for 14 consecutive days, followed by 7 days of rest, and every 21 days counts as a cycle. According to the syndromes of the patients, XSLJZD was given combined treatment. The detailed composition of XSLJZD is as follows: Radix codonopsis 15 g, Rhizoma atractylodis macrocephalae 20 g, Poria 15 g, Pericarpium citri reticulatae 15 g, 10 g of Pinellia tuber, 10 g of Radix aucklandiae, 10 g of Fructus amomi, and 6 g of Radix glycyrrhizae.

### Outcome measurements

2.8

#### Primary endpoint

2.8.1

The primary endpoint is PFS, the time from randomization to disease progression (Evaluation of tumor progression about RECIST 1.1) or death.

#### Secondary endpoints

2.8.2

The secondary endpoint is overall survival (OS) and Quality of Life Assessment (QOLA). OS is defined as the time from randomization to death for any reason. The last follow-up time is usually calculated as the time of death for the participants who have lost the visit before death (Additional file 1; Additional file 2; Additional file 3; Additional file 4).

QOLA, including symptom improvement, KPS, and AE assessment before and after treatment, was performed for 1 to 3 days before each cycle of treatment, Details are as follows:symptom improvement, mainly observe the changes of common symptoms of GC and CRC (pain, diarrhea, fatigue, poor acceptance, sleep), refer to the “Guiding Principles for Clinical Research of New Chinese Medicine” in the relevant TCM symptom integral quantification table of MDASI-TCM, compared to the scores accumulated for each symptom, analyze the difference before and after treatment^[30]^; KPS, comparative analysis before and after the difference; assessment of AE (safety outcomes). Assessment and grading of AE were based on the Common Terminology Criteria for Adverse Events (CTCAE) Version 4.0,^[31]^ AEs include nausea and vomiting, granulocytopenia, thrombocytopenia, anemia, impairment of liver and kidney function, diarrhea, peripheral neuritis, stomatitis, hand-foot syndrome, and any other new symptoms or diseases related to or unrelated to intervention. SAEs refer to the events that must be hospitalized or prolonged, permanently and seriously disabled, life-threatening, or death in clinical trials. SAE will be reported to the chief researcher and the hospital ethics committee, and the experiment will be stopped within 24 hours.

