### Sample size estimate

2.12

The RCT is an advantage test that uses an appropriate formula to estimate the sample size. Based on the results of our preliminary observational study and expert advice, we assume a significant level of α = 0.05, test efficacy (1-β) = 80%, and a pooled standard deviation of 9.59. Considering 10% dropout rate, the total sample size is expected to be 256 (128 of each carcinoma type, 64 in each group).

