### Statistical analysis

2.13

Analysis for primary endpoint PFS and secondary endpoint OS: the median of PFS and OS in each group was counted. Survival curves were plotted using Log-Rank test and Kaplan–Meier survival analysis.

Analysis for Symptom Improvement Assessment: behavioral status scores before and after chemotherapy (KPS), repeated measure's analysis of variance before and after treatment in the group; TCM symptom scores before and after chemotherapy (MDASI-TCM), paired *t* test before and after treatment in the group. The *t* test was used for comparison between groups.

All these statistical analyses were performed with SPSS 23.0 (SPSS Inc, Chicago, IL). A 2-tailed *P* value <.05 was considered statistically significant.

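### Overall survival: the rule in section 2.8.2 dates death at last follow-up for participants lost to follow-up, so patients last known alive become deaths instead of censored observations

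*Protocol article*

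**What the plan says.** Section 2.8.2 makes OS a secondary endpoint: "OS is defined as the time from randomization to death for any reason". The next sentence gives the rule for patients lost to follow-up: "The last follow-up time is usually calculated as the time of death for the participants who have lost the visit before death". Nothing elsewhere in the article says that such patients are censored.

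Section 2.13 plans medians of PFS and OS and adds: "Survival curves were plotted using Log-Rank test and Kaplan–Meier survival analysis". Section 2.9 plans up to five years of follow-up and the recording of 3- and 5-year OS. Section 2.10.3 asks that survival status still be tracked when a participant refuses further visits, unless information is also refused.

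PFS is defined separately in section 2.8.1, counts death as an event, and has no rule for loss: "The primary endpoint is PFS, the time from randomization to disease progression" (or death). Section 2.12 allows for dropout in the sample size: "Considering 10% dropout rate, the total sample size is expected to be 256", that is "128 of each carcinoma type, 64 in each group".

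**The concern.** Kaplan–Meier and log-rank need two items per patient: a time, and whether the event occurred at that time. A patient who was alive at last contact and then lost has a known minimum survival time and no known death. Recording a death on that date adds an event that nobody observed, at a time when the patient was known to be alive.

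Every such entry pulls the survival curve down, so the absolute OS estimates are too low. The comparison between arms is also at risk, because the event rate then mixes mortality with loss. If one arm loses more patients, it appears to have worse survival.

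The word *usually* adds a second difficulty. It leaves open which lost patients are counted as dead, so the choice can be made case by case. Sections 2.1 and 5 call the trial open, while section 2.6 describes blinding. If allocation is known, discretion over who counts as dead is a direct route to bias.

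**Working it through.** **Inputs.** The article gives no median OS, hazard ratio, event count or expected loss of vital status, so there is no survival figure of the plan's own to reproduce. The only related figure is the 10% dropout allowance in section 2.12. It stands beside a standard deviation of 9.59, an input for comparing means, and is not described as loss of survival status. Ten per cent is therefore used below as an assumption. It would mean 0.10 × 128 = 12.8, about 13 patients per cancer type.

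The other assumptions are exponential OS, a control median of 18 months (range 12 to 24), and loss unrelated to prognosis.

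**1. Absolute OS, 10% actually lost within 60 months.**
- Death hazard: λ = ln 2 / 18 = 0.03851 per month.
- Loss hazard γ solves γ/(λ+γ) × [1 − exp(−60(λ+γ))] = 0.10, giving γ = 0.00467.
- With censoring, the estimated hazard is λ. Under the rule it is λ + γ = 0.04318.

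| Quantity | Censored | Lost = dead |
|---|---|---|
| Median OS (months) | 18 | 0.6931 / 0.04318 = 16.05 |
| 3-year OS | exp(−36 × 0.03851) = 25% | exp(−36 × 0.04318) = 21% |
| 5-year OS | exp(−60 × 0.03851) = 10% | exp(−60 × 0.04318) = 7.5% |

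For true medians of 12 and 24 months, the median under the rule is 10.77 and 21.21 months, a fall of about 10% and 12%. A simulation with 64 per arm agrees with these values.

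**2. Hazard ratio (HR), equal loss.** Under the rule, HR = (λ_T + γ_T)/(λ_C + γ_C).
- With the same loss hazard in both arms and a true HR of 0.70: (0.02696 + 0.00467)/(0.03851 + 0.00467) = 0.73.
- In a trial simulation (128 per arm, 24-month accrual in a 60-month study, nominal 10% loss spread uniformly over 24 months), 0.70 becomes 0.72.
- A true HR of 1.00 stays at 1.00.

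**3. Hazard ratio, unequal loss.** The same simulation uses nominal loss of 15% in one arm and 5% in the other. Because some patients die before they would be lost, realised loss is about 10% v 3%.

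| Arm with more loss | True HR | HR under rule | Effect at 128 per arm |
|---|---|---|---|
| Combination | 1.00 | about 1.08 | type I error 9–10% |
| S-1 alone | 1.00 | about 0.92 | type I error 9–10% |
| Combination | 0.70 | about 0.79 | power from 67–69% to 38–40% |

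At 64 per arm, the size planned within each cancer type, type I error in the null cases is about 7%.

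If 15% v 5% is the loss actually realised, the shift is larger. Solving for γ as in step 1 gives 0.00735 and 0.00223. A null HR becomes (0.03851 + 0.00735)/(0.03851 + 0.00223) = 1.13, or 0.89 in reverse, with type I error about 10% at 64 per arm.

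**The case against.** **The sentence may mean something narrower.** It could cover only patients known to have died whose date of death is unknown. That reading shortens some times but creates no false deaths. The English looks translated, and the sentence points to additional files that are not shown, so this cannot be ruled out. It is the less natural reading, and the words do not limit the rule to known deaths.

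**Few patients may be affected.** Section 2.10.3 keeps tracking survival after visits are refused, and stopping a decoction is not the same as being lost to survival follow-up. This stands as a reason to expect fewer lost patients. It does not change how those who are lost are counted.

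**Unequal loss is assumed.** No arm-specific loss figure appears in the article. Only one arm takes a decoction, which makes imbalance plausible but does not establish it. This stands: the bias in the comparison is mainly conditional on unequal loss.

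**Lost patients may be sicker.** If so, censoring is itself too favourable. That is a reason to run loss-as-death as a sensitivity analysis, not to use it as the main rule.

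**Primary endpoint.** A reader might infer that the rule also biases PFS, because PFS counts death. The article does not support this as a statement of fact. The rule appears only under OS, section 2.8.1 contains no loss rule, and section 3 bases the final evaluation on independent blinded imaging review. PFS would be affected only if the imputed death were carried into it, which the text neither states nor excludes.

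**Conclusion.** The OS rule is wrong as written and does not fit the planned analysis. What is certain is the direction of the effect on absolute survival: median, 3-year and 5-year OS are understated for any loss above zero. The size rests on assumptions outside the article. With 10% actually lost and a true median of 18 months, the median is about 2 months too short, 3-year OS about 4 percentage points too low and 5-year OS about 2.5 points too low.

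The treatment comparison is a conditional matter. Equal loss leaves the HR nearly unchanged; a marked imbalance can move a null HR by roughly 8 to 13% in either direction and raise type I error above 5%. The defect as stated concerns a secondary endpoint. The article does not show that it reaches PFS.

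**What to change.** Replace the sentence in section 2.8.2 with: *Participants not known to have died are censored for OS at the date last known alive.* Drop *usually*, so that one rule applies to every participant.

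Add a statement that loss to follow-up does not by itself create a PFS event. If the sentence was meant only for patients known to have died on an unknown date, say so and give the dating rule for those cases.

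Keep loss-as-death only as a labelled sensitivity analysis for OS, reported with the number lost in each arm.

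The cost is a few lines of text. No further data collection is needed, since the last follow-up date is already the quantity the present rule uses. The change should be made before the survival data are analysed.

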### Follow-up

2.9

This study is expected to last for 5 years. Each patient will be followed until death or withdrawal from the study. Follow up frequency: follow up every 28 ± 3 days in the first year of the study, and record the PFS; then follow-up every 3 months and record the OS of 3 year and 5 year.

A detailed schedule of the study is presented in Table 1.

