#### Withdrawal criteria

2.10.2

The withdrawal criteria are as follows: participants voluntarily request to withdraw from the test; SAE closely related to drugs occur, and toxicity intolerance makes the test impossible to continue; no reason for delaying treatment for >2 weeks; it cannot be treated according to the program, poor compliance; considering the interests of the participants, the researchers believe that the best choice is to terminate the study treatment.

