#### Solution

2.10.3

If the participant does not appear as planned during the follow-up period, the researcher shall know the reason as much as possible, record the reason on the case report form (CRF), contact the participant as much as possible to ask the participant to conduct a final visit, record the last medication time, try to complete the effectiveness and safety inspection when withdrawing from the study as specified in the scheme, and complete the safety follow-up period. AE and outcomes were fully recorded. According to the actual situation of the participants, researchers can suggest or provide new or alternative treatment methods to the participants.

If the participant is asking for termination of the study, researchers will retain the data and must follow-up in the specific follow-up steps specified in the study. If the participant refuses to visit further, he or she should continue to track his or her survival status unless the participant refuses to disclose further information or is contacted. In this case, no further research evaluations should be conducted, and no further information should be collected. The study sponsor may retain and continue to use all the information before the withdrawal of the participant's informed consent, unless the participant requests that the collected information be withdrawn.

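### The OS rule in section 2.8.2 turns patients lost to follow-up into deaths; they should be censored at the date last known alive

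*Protocol article*

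**What the plan says.** Section 2.8.2 defines OS as the time from randomization to death from any cause. The rule for patients who are lost follows: "The last follow-up time is usually calculated as the time of death for the participants who have lost the visit before death".

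Section 2.13 reports OS by medians ("the median of PFS and OS in each group was counted"), Kaplan-Meier curves and a log-rank test. Section 2.9 adds landmark figures after the first year: "then follow-up every 3 months and record the OS of 3 year and 5 year".

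On who stays under observation, section 2.9 says: "Each patient will be followed until death or withdrawal from the study". Section 2.10.2 lists as withdrawal not only the participant's own request but also drug toxicity ("SAE closely related to drugs occur, and toxicity intolerance makes the test impossible to continue"), treatment delay ("no reason for delaying treatment for >2 weeks"), poor compliance and the investigator's judgement ("considering the interests of the participants, the researchers believe that the best choice is to terminate the study treatment"). Section 2.10.3 covers participants who ask to stop: "If the participant is asking for termination of the study, researchers will retain the data and must follow-up". It also tracks survival for those who refuse visits, unless they refuse further information or cannot be contacted. For participants who miss planned visits it asks for contact, a final visit, efficacy and safety checks, and recording of outcomes.

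**The concern.** A patient who was alive at the last contact and then disappears has an unknown death date. Kaplan-Meier and log-rank methods handle this by censoring at the last date known alive. The rule in 2.8.2 instead records an event that was not observed. This is a stated rule, so it cannot be excused as detail left to an unseen analysis plan. The word *usually* makes it worse, because it leaves open when the rule applies and who decides.

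Two things are at stake. The first is the absolute OS results: the medians and the 3- and 5-year figures in each arm. The second is the comparison of arms if one arm loses more patients than the other. Some loss is foreseen: section 2.12 allows for 10% dropout, and 2.10.3 accepts that some participants will refuse any further information.

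**Working it through.** **Is there a figure to reproduce?** No. The article gives no OS median, OS loss rate or OS effect. The 10% dropout in 2.12 inflates a sample size built on a standard deviation of 9.59; it is not an OS loss rate. All OS inputs below are assumptions.

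**Step 1: direction.** Under the rule the recorded death date is the last contact. For a patient who was alive then, this cannot be later than the true death date. The OS curve under the rule is therefore at or below the curve with full follow-up, in each arm, whatever the loss pattern.

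**Step 2: size with equal loss.** Assume exponential OS with median m, and a share p assigned to loss, spread evenly over months 0 to 12 and unrelated to prognosis. A patient counts as alive at month t only if neither dead nor lost:

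S*(t) = 2^(−t/m) × (1 − p × min(t, 12)/12)

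When the recorded median falls after month 12, it solves 2^(−t/m) × (1 − p) = 0.5, so t = m × log2(2(1 − p)).

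- p = 0.10, m = 18: 18 × log2(1.8) = 18 × 0.848 = 15.3 months, 15% lower.
- p = 0.10, m = 24: 24 × 0.848 = 20.4 months, 15% lower.
- p = 0.10, m = 12: the median falls before month 12; solving the full formula gives 10.4 months, 13% lower.
- p = 0.05, m = 18: 18 × log2(1.9) = 18 × 0.926 = 16.7 months, 7% lower.

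After month 12 each landmark figure is multiplied by (1 − p). With m = 18 and p = 0.10:

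- 3-year OS: 2^(−36/18) = 25.0%, times 0.9 = 22.5%.
- 5-year OS: 2^(−60/18) = 9.9%, times 0.9 = 8.9%.

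**Step 3: unequal loss, no true effect.** Simulated trials used OS medians of 12, 18 and 24 months, 24-month accrual, a 60-month study and loss over months 0 to 12. Loss is given as S-1 / combination in percent; a hazard ratio (HR) below 1 favours the combination.

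*Loss unrelated to prognosis (64 or 128 per arm):*

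| Loss | HR, lost counted as dead | Log-rank error |
|---|---|---|
| 10/10 | 1.00 | 5.0–5.4% |
| 6/4 | 0.98 | 5.1–5.8% |
| 7.5/2.5 | 0.94–0.96 | 5.7–7.1% |
| 15/5 | 0.89–0.92 | 7.4–12.5% |
| 5/15 | 1.08–1.13 | 7.2–13.4% |

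Censoring the same losses gives HR 1.00–1.01 and error 4.9–5.8%.

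*All losses from a poor-prognosis fifth with 2 to 3 times the hazard (128 per arm):*

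| Loss | HR, lost counted as dead | HR, lost censored |
|---|---|---|
| 7.5/2.5 | about 0.97–0.99 | about 1.02–1.04 |
| 15/5 | about 0.94–0.98 | about 1.03–1.05 (up to 1.06 in one run) |

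In this second setting neither rule is free of bias. The two err in opposite directions and by similar amounts, so only better follow-up removes the problem.

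**The case against.** The strongest reply is that the figures for the arm comparison rest on unsupported inputs. No loss rate for survival status is given, and 2.10.3 keeps participants who ask to stop under follow-up, so real loss should be below the 10% dropout. Nothing in the article supports a 15/5 split. At 6/4 the shift is trivial, and with equal loss there is no HR bias when there is no true effect. If losses come from sicker patients, counting them as dead is less wrong than the first table suggests, and censoring is itself biased. All of this stands, and it limits what can be claimed about the comparison. It does not rescue the rule, whose effect on medians and landmark OS needs no imbalance.

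A second reply is that the wording may be a poor rendering of ordinary censoring. That is possible, but the sentence says the opposite and would need correcting anyway.

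Three stronger readings are tempting and are not supported:

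- *The rule favours the combination.* The introduction expects the herbal treatment to reduce chemotherapy toxicity, so S-1 alone might lose more patients. But an added decoction could equally raise non-compliance, and the bias would then reverse.
- *Patients stopped by the investigator leave follow-up by design.* Sections 2.9 and 2.10.2 can be read that way. However, the last criterion in 2.10.2 ends study treatment, which need not end follow-up; 2.10.3 seeks contact, a final visit and outcomes from non-attenders; and Table 1 and the additional files are not shown. The reading rests largely on the silence of a condensed article.
- *The primary PFS comparison is compromised.* The rule is attached to OS, and the article does not extend it to PFS.

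**Conclusion.** The OS rule in 2.8.2 is wrong as written. It contradicts the OS definition in the same section and the survival methods in 2.13. That it pulls OS downwards is certain wherever it is applied to a patient who was alive at last contact. How far depends on assumptions: with exponential survival and loss unrelated to prognosis, 10% loss in the first year lowers the median by 13 to 15% and cuts 3- and 5-year OS by a tenth of their value; 5% loss lowers the median by about 7%. Loss concentrated in sicker patients would make the understatement smaller.

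Bias in the comparison of arms is possible but of unknown size and direction. The HR of 0.89–0.92 at 15/5 is an upper illustration for loss unrelated to prognosis, not an expected result, and censoring would not be unbiased if loss is related to prognosis. OS is a secondary endpoint, and *usually* leaves it unknown how often the rule would apply. The point should be corrected before analysis, but it does not call the trial design into question.

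**What to change.** 1. In 2.8.2, replace the sentence with a rule that participants not known to have died are censored for OS at the date last known alive. Drop *usually*, so that one rule applies to everyone.
2. As a supporting clarification in 2.9 and 2.10.3, state that stopping study treatment for any reason in 2.10.2 does not end follow-up for progression and survival, unless the participant withdraws consent to follow-up. This also limits prognosis-related loss, which censoring cannot repair.

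The first change costs nothing beyond a short amendment with ethics notification. The second adds visits and imaging for patients taken off treatment. If the planned dropout is a guide, that is at most about 26 patients (0.10 × 256 = 25.6), or about 13 if half of them stop at their own request and are already covered by 2.10.3 (an assumption). No extra recruitment is needed.

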#### Other measurements

2.8.3

Baseline was defined as pre chemotherapy (−7 to 0 days). During baseline examination, the patient's gender, age, marital status, education level, comorbidity, pathological type, tumor staging, radiotherapy and chemotherapy regimen, and medication records for the past 3 months will be recorded.

### Follow-up

2.9

This study is expected to last for 5 years. Each patient will be followed until death or withdrawal from the study. Follow up frequency: follow up every 28 ± 3 days in the first year of the study, and record the PFS; then follow-up every 3 months and record the OS of 3 year and 5 year.

A detailed schedule of the study is presented in Table 1.

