Based on the above consideration, we designed the study of XSLJZD combined with S-1 in the maintenance therapy of stage III or IV GC and CRC. It is an open, single-center, and randomized trial, which aims to determine the efficacy and safety of S-1 combined with XSLJZD in the maintenance therapy of stage III or IV GC and CRC. In addition, this study also provides meaningful clinical information for this combination model of chemotherapeutic drugs and TCM, laying the foundation for larger clinical trials in the future. However, the study has several limitations. First, this is a single-center trial, which is more difficult to recruit than multicenter trials. Therefore, it will take longer to recruit if enough samples are recruited. Second, although TCM formulas have been widely used in clinical practice in China, RCT with a well-designed and long-term follow-up is still lacking. Consequently, the results of the RCT will provide experience and evidence for developing guidelines and policies for facilitating the reasonable use of TCM formulas. We also hope that this research will open a new direction for the treatment of patients with stage III or IV GC and CRC.

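### The follow-up text ties PFS recording to the first year and names only OS afterwards, which conflicts with a PFS endpoint that has no time limit; whether the 5 years include accrual is also unstated

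*Protocol article*

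**What the plan says.** All references are to the protocol article.

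- **Primary endpoint (2.8.1).** "The primary endpoint is PFS, the time from randomization to disease progression" (by RECIST 1.1) or death. No time limit is given.
- **Follow-up (2.9), visits and what is recorded.** Visits start at intervals of about four weeks, and the sentence continues: "days in the first year of the study, and record the PFS; then follow-up every 3 months and record the OS of 3 year". OS at 5 years is named as well.
- **Follow-up (2.9), duration.** "This study is expected to last for 5 years". The next sentence reads: "Each patient will be followed until death or withdrawal from the study".
- **Secondary endpoints (2.8.2).** "OS is defined as the time from randomization to death for any reason".
- **Study design (2.1).** Both groups receive their treatment for 5 years, the same length as the whole study.
- **Discussion (5).** On single-centre recruitment: "Therefore, it will take longer to recruit if enough samples are recruited". No accrual period is given.
- **Statistical analysis (2.13).** Median PFS and OS per group, Kaplan-Meier curves and the log-rank test, with no truncation at 12 months.
- **Protocol monitoring (3).** A blinded independent committee reviews imaging throughout the trial, and the final evaluation rests on its reading.

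Table 1, the detailed visit schedule, is not visible in the text available for review.

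**The concern.** Section 2.9 names one endpoint for each phase of follow-up: PFS in the first year, OS after it. A site that follows this wording could stop documenting progression after year 1 in patients who are still progression-free and possibly still on treatment. Their later progression would then be missing. If they died later, the death date would stand in for an earlier progression: a patient who progressed at month 15 and died at month 24 would be given a PFS of 24 months.

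The primary log-rank comparison would lose events or use wrong dates, and a group median beyond 12 months would be poorly supported. Progression dates that were never collected may not be recoverable.

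Two further gaps lie in the same section. The year is counted from the study, whereas PFS is counted from randomization. And a 5-year OS is promised from a study of 5 years without separating accrual from follow-up.

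**Working it through.** **The plan's own figures.** The plan gives no median PFS, hazard ratio, event number, accrual period or minimum follow-up, so there is no PFS figure to reproduce. The Sample size section (2.12) gives a pooled SD of 9.59 and no difference. Solving backwards for 64 per group, two-sided alpha 0.05 and 80% power gives 9.59 × (1.960 + 0.842) × √(2/64) = 4.75 points on a continuous scale. That says nothing about PFS events or the follow-up they need. Medians, hazard ratios and accrual periods below are therefore assumptions.

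**Step 1. Patients still event-free at 12 months.** Exponential PFS with median m months: S(t) = 2^(−t/m).

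| Assumed median | S(12) | S(60) | Share of events by month 60 that fall after month 12 = [S(12) − S(60)] / [1 − S(60)] |
|---|---|---|---|
| 6 | 25% | 0.1% | 25% |
| 9 | 40% | 1.0% | 39% |
| 12 | 50% | 3.1% | 48% |

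**Step 2. Upper bound on the loss of events and power.** Take 230 evaluable patients (256 × 0.90 = 230.4), both tumour types pooled, 1:1 allocation and an assumed HR of 0.70.

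- Events by time T: 230 × {1 − ½[2^(−T/m) + 2^(−0.70T/m)]}, with m the median on S-1 alone.
- Schoenfeld power: Φ(½√events × |ln HR| − 1.960), with |ln 0.70| = 0.357.

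Example, m = 9 and T = 12: 230 × {1 − ½[0.397 + 0.524]} = 124 events; ½ × √124 × 0.357 − 1.960 = 0.03, so power is 51%.

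| S-1 median | Events, 12-month cut | Power | Events, 36 months | Power |
|---|---|---|---|---|
| 6 | 158 | 61% | 222 | 76% |
| 9 | 124 | 51% | 206 | 73% |
| 12 | 102 | 44% | 189 | 69% |

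For one tumour type alone (128 patients, no dropout taken off, assumed HR 0.60, S-1 median 9 months), there are about 66 events by month 12 (power about 55%) against about 123 by month 60 (power about 81%).

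These losses are upper bounds, because every event after month 12 is counted as lost and section 2.9 would still capture later deaths. The 36-month column is also generous, since it gives all 230 patients a full 36 months of follow-up.

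**Step 3. OS at 5 years.** If the 5 years include accrual lasting A months, the last patient has at most 60 − A months of follow-up: 48 for A = 12, 36 for A = 24, 24 for A = 36. Only a patient randomized on the first day could reach 60 months. Potential follow-up of 36 months is available to everyone if A ≤ 24, and to 24/36 = 67% of patients if A = 36 with uniform accrual. If the 5 years are counted per patient, every survivor who stays in follow-up reaches 60 months and the difficulty disappears.

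**The case against.** The strongest reply is that section 2.9 is loosely worded rather than wrong. Four parts of it deserve an answer.

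- **A reader might infer that all primary events after year 1 are lost.** The documents do not support this. Patients are followed until death or withdrawal, and death is a PFS event. No sentence forbids later tumour assessment, the committee reviews imaging throughout the trial, and the PFS analysis is not truncated. Table 1 may list later assessments. What stands is narrower: the prose assigns only OS to the later visits, and no visible sentence requires progression to be recorded there.
- **A reader might infer that patients enrolled after calendar year 1 have no PFS window.** With uniform accrual over 2 or 3 years that would be 12/24 = 50% or 24/36 = 67% of patients. The reading is strained. A 28-day visit interval makes sense from each patient's own start, and OS is measured from randomization. What stands is that the starting point should be stated.
- **A reader might infer that 5-year OS cannot be observed.** That holds only if the 5 years include accrual. Treatment for 5 years and follow-up until death also fit 5 years per patient. What stands is that the text does not say which.
- **The magnitude is assumed.** This is correct. The main calculation also pools tumour types, whereas section 2.12 sizes each at 64 per group.

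**Conclusion.** The point holds in a limited form. Section 2.9 conflicts with the primary endpoint in 2.8.1: followed as written, progressions after the first year may be missed or misdated, while deaths are still captured. With assumed exponential medians of 6 to 12 months, 25% to 50% of patients are event-free at 12 months, so the conflict touches a substantial part of the primary data. The fall in power (for example from 73% to 51% with an S-1 median of 9 months and HR 0.70) is the most that could be lost under those assumptions, not an estimate of what will be lost.

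Separately, the text leaves open whether the 5 years include accrual. If they do, almost no patient can reach 60 months, and a 5-year OS would rest on next to no patients at risk. If they are per patient, it is observable.

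**What to change.** Reconcile section 2.9 with 2.1, 2.8.1 and Table 1:

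1. Count the visit schedule from each patient's randomization.
2. State that progression status by RECIST 1.1 is recorded at the already scheduled 3-monthly visits, until progression or death.
3. State whether the 5 years are per patient or include accrual. If they include accrual, report Kaplan-Meier OS at 3 years and drop 5-year OS as a stated result.

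**Cost.** The first and third changes are wording. The second adds progression assessment to existing visits for patients still progression-free after year 1. If tumour assessment already continues after year 1, this too is only wording. If it does not, it means additional imaging and independent committee review for those patients. The sample size does not change.
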